## Abstract

**Background:**

Despite the positive outcomes of the use of noninvasive positive pressure ventilation (NPPV) in patients with acute exacerbation of chronic obstructive pulmonary disease (AECOPD), NPPV fails in approximately 15% of patients with AECOPD, possibly because the inspiratory pressure delivered by conventional low-intensity NPPV is insufficient to improve ventilatory status for these patients. High-intensity NPPV, a novel form that delivers high inspiratory pressure, is believed to more efficiently augment alveolar ventilation than low-intensity NPPV, and it has been shown to improve ventilatory status more than low-intensity NPPV in stable AECOPD patients. Whether the application of high-intensity NPPV has therapeutic advantages over low-intensity NPPV in patients with AECOPD remains to be determined. The high-intensity versus low-intensity NPPV in patients with AECOPD (HAPPEN) study will examine whether high-intensity NPPV is more effective for correcting hypercapnia than low-intensity NPPV, hence reducing the need for intubation and improving survival.

**Methods/design:**

The HAPPEN study is a multicenter, two-arm, single-blind, prospective, randomized controlled trial. In total, 600 AECOPD patients with low to moderate hypercapnic respiratory failure will be included and randomized to receive high-intensity or low-intensity NPPV, with randomization stratified by study center. The primary endpoint is NPPV failure rate, defined as the need for endotracheal intubation and invasive ventilation. Secondary endpoints include the decrement of arterial carbon dioxide tension from baseline to 2 h after randomization, in-hospital and 28-day mortality, and 90-day survival. Patients will be followed up for 90 days after randomization.

**Discussion:**

The HAPPEN study will be the first randomized controlled study to investigate whether high-intensity NPPV better corrects hypercapnia and reduces the need for intubation and mortality in AECOPD patients than low-intensity NPPV. The results will help critical care physicians decide the intensity of NPPV delivery to patients with AECOPD.

**Trial registration:**

ClinicalTrials.gov, NCT02985918. Registered on 7 December 2016.

**Electronic supplementary material:**

The online version of this article (10.1186/s13063-018-2991-y) contains supplementary material, which is available to authorized users.

## Background

Chronic obstructive pulmonary disease (COPD) is a common, preventable, and treatable disease, characterized by persistent respiratory symptoms and limited airflow [1]. Based on the Burden of Obstructive Lung Disease program and other large-scale epidemiological studies, there were 384 million patients with COPD worldwide in 2010, with a global prevalence of 11.7% [1, 2]. Remarkably, COPD is currently the fourth leading cause of death in the world and is projected to be the third leading cause by 2020, resulting in an economic and social burden that is both substantial and increasing [1, 3, 4]. Acute exacerbation of COPD (AECOPD) is defined as an acute worsening of respiratory symptoms resulting in additional therapy, and it is characterized as an acute clinical event that negatively affects health status and hospitalization and readmission rates, and it may even increase the rates of comorbidities and COPD-related mortality [1, 5, 6]. Hence, it is of great importance to investigate effective treatments or enhance current therapeutic measures for improving prognosis.

Over the past two decades, noninvasive positive pressure ventilation (NPPV) has been increasingly used in the care of patients with AECOPD [7–11]. Several lines of evidence strongly support its use in these patients [12]. Numerous previous studies [13–19] have indicated that NPPV corrects ventilatory status, reduces the need for invasive ventilation, and improves prognosis more than conventional oxygen therapy. However, NPPV still fails in approximately 15% of AECOPD patients; in this group, mortality is not reduced [18–20]. There are several possible reasons for this. First, in the conventional approach, in which a relatively lower inspiratory positive airway pressure (IPAP) is used, termed low-intensity NPPV, pH and arterial carbon dioxide tension (PaCO_2_) continuously worsen, and it becomes difficult to recover consciousness in a small proportion of AECOPD patients, in spite of NPPV use [20–22]. Second, although PaCO_2_ can be decreased through the use of conventional NPPV in the majority of AECOPD patients, it is still difficult to normalize ventilatory status, and it can easily worsen if there is a slight change in a patient’s clinical situation, which may trigger NPPV failure [16, 19]. Third, if PaCO_2_ is not decreased to a normal level, it might have a harmful effect on the internal environment and vital organs. Finally, for a minority of AECOPD patients, NPPV is poorly tolerated and must be discontinued, possibly because of the inadequate pressure support provided by low-intensity NPPV; this ultimately requires endotracheal intubation [23, 24].

High-intensity NPPV, a form of pressure-limited ventilation, combined with stepwise titration of IPAP up to 30 cmH_2_O, was introduced as a novel therapeutic option in an attempt to maximally decrease elevated PaCO_2_ to normal levels [25, 26]. In theory, high-intensity NPPV may be more efficient than low-intensity NPPV in augmenting alveolar ventilation and offsetting the extra dead space caused by the face mask, and it can reduce the inspiratory work of breathing and alleviate dyspnea, bringing greater comfort and tolerance. Windisch et al. [27] reported that, in patients with stable hypercapnic COPD, improvements in PaCO_2_, lung function, and breathing pattern were achievable using high-intensity NPPV. Dreher et al. [28], in a study on patients with stable hypercapnic COPD, directly compared high-intensity NPPV (mean IPAP of 29 cmH_2_O) with the conventional approach, which uses a considerably lower IPAP (mean of 15 cmH_2_O), and found that high-intensity NPPV was superior to low-intensity NPPV in controlling nocturnal hypoventilation, thus improving lung function, dyspnea during physical activity, and health-related quality of life. However, to the best of our knowledge, it remains unclear whether high-intensity NPPV is superior to low-intensity NPPV in improving ventilatory status (and thus reducing the need for intubation and mortality rate) in patients with AECOPD.

We hypothesize that high-intensity NPPV will be more effective for correcting hypercapnia than low-intensity NPPV, thereby reducing the need for intubation and improving survival in AECOPD patients. Accordingly, the high-intensity versus low-intensity NPPV in patients with AECOPD (HAPPEN) study will be performed to assess the efficacy of high-intensity NPPV in the care of AECOPD patients in comparison with low-intensity NPPV.

## Methods/design

### Aims

The primary aim of the HAPPEN study is to determine whether high-intensity NPPV is more effective for correcting hypercapnia than low-intensity NPPV in patients with AECOPD. The secondary aim is to determine whether high-intensity NPPV is more effective than low-intensity NPPV for decreasing PaCO_2_ from baseline to 2 h after randomization and hospital mortality, and improving 28-day mortality and 90-day survival.

### Study design

The HAPPEN study is a multicenter, two-arm, single-blind, prospective, randomized controlled trial initiated by the investigators of the HAPPEN collaboration group. In total, 600 AECOPD patients with low to moderate hypercapnic respiratory failure admitted to a network of 27 respiratory wards from university hospitals in China will be included and randomized to receive high-intensity or low-intensity NPPV. The protocol structure was written in compliance with the Consolidated Standards of Reporting Trials (CONSORT) 2010 statement guidelines, and it follows the Standard Protocol Items: Recommendations for Interventional Trials (SPIRIT) 2013 statement. The CONSORT diagram of the study is shown in Fig. 1, and the SPIRIT schedule for this trial is given in Fig. 2. The complete SPIRIT checklist for the study is provided in Additional file 1.

**Fig. 1 Fig1:**
[figure not shown]
CONSORT diagram. *AECOPD* acute exacerbation of chronic obstructive pulmonary disease, *NPPV* noninvasive positive pressure ventilation, *V*_*T*_ tidal volume, *IPAP* inspiratory positive airway pressure

**Fig. 2 Fig2:**
[figure not shown]
SPIRIT schedule of enrollment, intervention, and assessments. *APACHE* Acute Physiology And Chronic Health Evaluation, *NPPV* noninvasive positive pressure ventilation, *GCS* Glasgow coma scale *ICU* intensive care unit

The trial was designed in accordance with the fundamental principles set forth in the Declaration of Helsinki and the requirements established by Chinese legislation in the field of biomedical research for the protection of personal data and concerning bioethics. The protocol has reached version 6, in which there were no further changes. The approval of the final protocol by the ethics committee at each participating center was obtained before recruitment was initiated. For inclusion in the study, signed written informed consent will be obtained from the patients, patients’ next of kin, or other surrogate decision makers, if appropriate (see Additional file 2). The study was registered on December 7, 2016 at https://ClinicalTrials.gov with identification number NCT02985918.

### Study population

During screening and prior to enrollment in the study, patients will be considered eligible for the study if they are diagnosed with AECOPD as defined by the criteria of the Global Initiative for Chronic Obstructive Lung Disease (GOLD) in 2017, with arterial pH < 7.35 and ≥ 7.25, and PaCO_2_ > 45 mmHg [1].

Patients will be excluded from study participation if any of the following criteria are present: age < 18 years; excessive amount of respiratory secretions or weak cough; upper airway obstruction; recent oral, facial, or cranial trauma or surgery; recent gastric or esophageal surgery; severe abdominal distension; active upper gastrointestinal bleeding; cardiac or respiratory arrest; pH < 7.25; arterial oxygen tension/fraction of inspired oxygen (PaO_2_/FiO_2_) < 150 mmHg; pneumothorax; severe ventricular arrhythmia or myocardial ischemia; severe hemodynamic instability despite fluid repletion and use of vasoactive agents; severe metabolic acidosis; lack of cooperation; and refusal to receive NPPV [29]. Patients will also be excluded if they have a do-not-intubate order or refuse research authorization.

### Recruitment

Investigators are screening consecutive patients with AECOPD every day at the 27 respiratory wards. This screening started in December 2017, and a recruitment time of 12 months has been estimated, based on the estimation of the incidence of AECOPD and patient characteristics at the first author’s hospital. Demographic data for screened patients are being recorded regardless of whether the patients meet the enrollment criteria. All are being reviewed with respect to all inclusion and exclusion criteria.

If patients meet all inclusion criteria and no exclusion criteria, the investigators will explain the nature and the aim of the study to the patients; if patients express an interest in participating, investigators will ask them to sign the informed consent form (see Additional file 2). Patients who meet all inclusion criteria and no exclusion criteria and sign the informed consent form will be included in the study.

### Randomization and blinding

Randomization will be accomplished by a computer-generated random number sequence, stratified by study center, with an allocation ratio of 1:1 for each group. The generation of sequences and their storage will be managed by an independent information technology expert who is not involved in this study. Each allocation sequence will be concealed from the coordinating center through the use of numbered, opaque, and sealed envelopes, and will be managed by an independent employee at the coordinating center who is not involved in this study. The randomization number will consist of a patient identification number of nine digits, in which the first four digits correspond to the identifier of the study center, the middle three correspond to the patient inclusion number at the respective center, and the remaining two correspond to the NPPV-strategy identifier. An independent telephone-contact system will be used for randomization. All investigators at each of the participating centers will immediately contact an independent employee of the coordinating center to obtain a randomization number if a patient fulfills the inclusion criteria. Within 1 h of the validation of the inclusion criteria, patients will be randomly assigned to undergo either high-intensity or low-intensity NPPV. Patients will continue to receive their current therapy prior to randomization assignment.

At each study center, at least two investigators will be conducting the study: one to perform the interventions defined in the protocol, and the other, who will be blinded to the intervention, to perform the data collection. All data related to the NPPV parameters will be extracted from a cloud platform by an independent information technology expert not involved in this study; all data analyses will be performed in a blinded fashion.

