### Data collection and definitions

At each study center, patient data will be collected using that center’s dedicated pseudonymous CRF, and the CRFs will be stored in locked file cabinets in areas with limited access. Data will be transmitted to the coordinating center whenever a patient dies or is discharged from the hospital, and follow-up data will be transmitted to the coordinating center when follow-up is complete. In addition, the coordinating center will have direct access to the cloud platform to extract the data related to the NPPV parameters. Before the data are exported into a computerized database at the coordinating center, two trained data collectors from the coordinating center will check the completeness and quality of information. Logical checks will be performed for missing data and to determine inconsistencies. If required, the data collector will contact the investigator by phone to validate or reformat the data for entry into the database. Then all data entry will be performed separately by two trained data collectors, and their work will be checked by another two collectors. Only the principal investigator and the data managers at the coordinating center will have access to the final database.

At enrollment, patients’ baseline characteristics will be recorded: demographics, medical history, history of NPPV use, history of steroids and/or inhalation therapy use, smoking status, spirometry (forced ventilatory capacity and forced expiratory volume in 1 s), Acute Physiology And Chronic Health Evaluation (APACHE) II score, vital signs (including heart rate, RR, arterial blood pressure, SpO_2_), dyspnea score, scale for the use of accessory muscles, Glasgow coma scale (GCS) score, arterial blood gases (including pH, PaO_2_, PaCO_2_, bicarbonates, and lactates), and routine laboratory tests (including hemoglobin, white blood cell count, platelet count, prothrombin time, partial thromboplastin time, creatinine, blood urea nitrogen, alanine aminotransferase, aspartate aminotransferase, and bilirubin).

At 2, 6, 24, and 48 h after randomization, vital signs, dyspnea score, scale for the use of accessory muscles, GCS score, supplemental oxygen flow, and arterial blood gases will be recorded.

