### Trial organization

Appendix 1 lists the investigators of the HAPPEN collaboration group. The steering committee is composed of the principal investigators in the study, who all contributed to its design and approved the final protocol (Appendix 2). The executive committee is made up of the main investigators at each participating center and is responsible for administrative, trial, and data management (Appendix 2). When the report on the results of the trial is submitted for possible publication, each study center will be eligible for one co-authorship, plus a further co-authorship for every 20 patients with complete datasets.

The DSMB is composed of three external, independent experts in critical care medicine, NPPV, and COPD (Appendix 2). At the interim analysis, using the general data provided by the three internal members, it will recommend the continuation or discontinuation of the trial, based on the available data from the interim analysis. The DSMB will be responsible for monitoring patient data and safety, including review of the protocol, with emphasis on data integrity and participant risk and safety issues, monitoring adverse events (including suspected severe adverse reactions), and monitoring the overall status of the study (e.g., progress of patient enrollment, general adherence to protocol, and completeness of data entry).

The trial management team includes a chief investigator, a project manager, a statistician, a clinical epidemiologist, and an investigator expert in clinical trials (Appendix 2). The responsibilities of this team are as follows:Planning and conducting the study: designing the protocol and CRF, designing the investigator manual, and managing and controlling data qualityResearch center support: assisting the centers with administrative submission, monitoring recruitment rates, providing sealed randomization envelopes, taking actions to increase patient enrollment, monitoring follow-up, auditing, and sending study materials to the research centersProducing a monthly study newsletter and developing supporting material for the studyProgramming a research-in-progress meeting at least once every 6 months with the principal investigators from all sitesStatistical analysis and research reporting: interim and complete statistical analysis and helping to write the final manuscript.

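### The patient identification number embeds an arm identifier that the protocol article does not withhold from the blinded data collector, and two further statements conflict with its blinding and interim safeguards

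*Protocol article*

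**What the plan says.** Under Randomization and blinding the article states: "The randomization number will consist of a patient identification number of nine digits". Four digits identify the centre, "the middle three correspond to the patient inclusion number at the respective center", and "the remaining two correspond to the NPPV-strategy identifier". Site investigators obtain this number by telephone from an independent employee of the coordinating center.

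The same section has at least two investigators per centre, one delivering the intervention and "the other, who will be blinded to the intervention, to perform the data collection". It has ventilator parameters extracted from the cloud platform by an independent information technology expert, and adds that "all data analyses will be performed in a blinded fashion". The Discussion concedes that treating investigators cannot be blinded and that this could cause bias. It answers with the blinded collector and the blinded extraction and analysis.

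Two later statements bear on the same safeguards:

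- Data collection and definitions: "the coordinating center will have direct access to the cloud platform to extract the data related to the NPPV parameters".
- Trial organization lists "interim and complete statistical analysis" among the tasks of the trial management team, which includes the chief investigator. Sample-size calculations and interim analyses says that the independent data and safety monitoring board performs the interim analysis.

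**The concern.** A patient identifier normally travels with the data, on forms, in queries and in the database. If it carries the arm, whoever handles it can learn the allocation or at least sort patients into two groups. The person at risk is the site data collector, who is meant to be blinded. The dyspnea score and the accessory-muscle scale involve judgement, and knowing the arm could colour them.

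The other two statements touch the coordinating center and trial leadership. Pressures and tidal volumes can disclose the arm without any code. Comparative interim results held by people who run the trial could influence its second half. Because the Discussion uses the blinded roles as its answer to an unblinded intervention, the text describing them should be consistent.

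**Working it through.** No power or sample-size figure is involved. The check sets the statements side by side.

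**1. What the two arm digits add.** The digit count is consistent: 4 + 3 + 2 = 9. Centre and inclusion number take 4 + 3 = 7 digits. Three digits give 10³ = 1,000 values per centre, against 600 patients planned in the whole trial, and four digits are ample for 27 centres. Seven digits therefore identify every patient, and the last two add only the allocation.

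**2. Who may see the number.** The article says that all investigators at each centre contact the independent employee to obtain it, and does not exempt the blinded one. Data collection and definitions calls the case report form pseudonymous without naming the code on it. No other patient code is described, and nothing says that the last two digits are masked or dropped.

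**3. How much could be revealed.** The design has two arms, "stratified by study center, with an allocation ratio of 1:1 for each group". If the code is constant within an arm, identifiers fall into two sets even without the key, and one known allocation labels both. The extent depends on facts the article does not give, so these are assumptions:

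| Assumption | Records labelled by one known allocation |
|---|---|
| Arm digits kept off forms and database, or a code unrelated between patients | none beyond that patient |
| Full number on forms, code constant within a centre but different between centres | that centre's patients, on average 600 / 27 ≈ 22 |
| Full number on forms and in the database, code constant across centres | about 22 for a site collector; up to 600 for someone who sees all centres |

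**4. Analyst.** A two-group comparison needs a group variable. A label whose key is withheld is compatible with blinded analysis, and nothing says that the analyst holds the key. The identifier is therefore a weaker threat here.

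**5. Ventilator data.** Randomization and blinding gives extraction to an expert outside the study; Data collection and definitions gives the coordinating center direct access for the same purpose. The variables include peak inspiratory pressure and exhaled tidal volume. The inspiratory pressure limit is 20 cmH₂O in one arm and 30 cmH₂O in the other, with tidal volume targets of 10 and 15 mL/kg. Both arms start at 10 cmH₂O, so lower values do not settle the arm, but a pressure clearly above 20 points to the high-intensity arm. Masking the identifier would not close this route.

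**6. Interim analysis.** One section has the independent board perform it after the first 300 randomized patients are discharged from hospital. Trial organization gives interim statistical analysis to the management team, and also says that three internal members supply general data to the board. The sections do not settle who sees results by arm.

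**The case against.** The strongest reply is that the article never says where the nine-digit number is used. It is described as what the site obtains at randomization, when somebody there must learn the arm. Two digits allow 100 codes for two arms, so the code could be masked or varied, and labelling of the forms may be set out in the full protocol. This stands as a limit on the size of the point. It does not remove the point, because the article itself defines the patient identifier as containing the arm and sets no limit on its use.

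A second reply concerns consequences, and most of it stands. Under NPPV weaning and failure, the attending physician makes the final intubation decision against written criteria, so the collector does not decide the primary endpoint. The dyspnea score, accessory-muscle scale and tolerance are not in the endpoint list. Mortality, hospital stay, costs and readmission depend little on the collector's judgement. Patient blinding and the concealed allocation sequence also remain.

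Third, the further statements might be read together: the independent expert may work through the coordinating center's access, and the team's statistician may only prepare material for the board. Both readings are possible, but the article states neither. That the chief investigator will see comparative results, or that this would shift intubation decisions, is not stated and is not claimed here.

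**Conclusion.** The point holds in a limited form. The identifier as described contains the arm, is the only patient code described, and conflicts with the stated blinding of the data collector. The risk to the analyst is smaller. Two further pairs of statements conflict, on who extracts ventilator data and on who carries out the interim analysis.

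A reader might infer that the collector and analyst can read the allocation off all 600 records and that blinding does not exist. The documents do not support that. It would need the full number on every record and a code that is readable and constant across the 27 centres, none of which is stated. The extent of unblinding is unknown; under the assumptions tabulated above it runs from none to all records.

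Nor would correcting the identifier remove the main route of bias for the primary endpoint, the unblinded attending physician's intubation decision, which the article openly acknowledges. The case for change is that the arm digits serve no identifying purpose and are easy to remove.

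**What to change.** - **Identifier.** Use only the seven-digit centre and inclusion number on case report forms, in the database and in correspondence. Keep the strategy code in a separate list held by the independent employee or the information technology expert until database lock, and give the analyst dummy arm labels.
- **Ventilator data.** Limit extraction of ventilation parameters to the independent expert named under Randomization and blinding, and amend Data collection and definitions to match.
- **Interim analysis.** Remove the interim analysis from the management team's tasks, and state that results by arm go only to the monitoring board. State also what the three internal members may supply and see. The board is described as three experts in critical care, noninvasive ventilation and COPD, so a statistician outside the management team may have to be named to run the comparison.

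The cost is a small amendment, relabelling of identifiers already issued and perhaps some independent statistical time at the interim. No extra patients or visits are needed. Recruitment began in December 2017, so relabelling cannot re-blind data already collected. If the full number has been on the forms, the trial report should say so and give the date of the change.
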